## Methods and analysis

### Aims

First, the GENESIS study aims to document changes in body composition and the contribution of the main metabolically active tissues (skeletal muscular tissues, adipose tissues, liver, heart, spleen, kidneys, and brain) to the metabolic switch during a 12-day fasting period. Changes in the size and mass of organs will be quantified. We hypothesize that a re-expansion and regeneration will follow a transient decrease of organ volume during fasting up to 4 months after food reintroduction. Protein resynthesis upon food reintroduction might correspond to an acceleration of the physiological protein turnover, which will be evaluated by measuring nitrogen excretion. Additionally, the organs’ specific compositions, especially the fat components, and their function will be documented along the fasting process. We hypothesize that these multi-system changes are safe, and that they could also be reflected by an improved cardiac and skeletal muscle metabolism and mitochondrial oxidative capacity which will be investigated by spiroergometry.

Second, the study focuses on fat storage, function, and exchange in adipose tissue, liver, spleen, kidney, and splanchnic tissue. Among the lipids studied, we focus on cholesterol metabolism during fasting, particularly sub-types of HDL, but also CEC and fatty acid profiles in the erythrocyte membrane.

Third, we will measure PBMC metabolome profiles to reveal cellular metabolic changes in circulating, easily accessible immune cells.

Fourth, we will determine whether persulfidation, which contributes to the maintenance of cellular oxidative functions, changes during fasting.

Last, we will measure if various metabolic and physiological changes, as described above, correlate to individual gut microbiota profiles. The composition and function of the fecal microbiota will be evaluated during LF using shotgun metagenomics. This will help us understand how intestinal microorganisms are linked to human physiology during fasting.

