### Study design

The GENESIS study is a prospective, monocentric, single-arm interventional study using a two-stage design. A total of 100 subjects will be included (Figure 2). The first 32 participants will undergo an augmented examination plan, including MRI/MRS scans to evaluate body composition changes at four time points: prior to and at the end of 12 fasting days, 1 and 4 months post fasting. This sub-cohort is statistically powered for detecting changes in whole body composition. Sixty-eight additional subjects will then be included for gut microbiota and lipid profile analyses. The study follows the STROBE guidelines (42).

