### Sample size calculation

The required sample sizes vary between the outcome parameters. Previously, the effect size in matched subjects was 0.81 for T2 relaxometry in muscles (55). Using these assumptions, the minimal sample size requirement is 14 to detect meaningful acute changes in muscle physiology (alpha = 0.05, power = 0.80). MRS studies monitoring triglyceride (TG) content during CR (83, 84) observed that effect sizes were 1.09 and 0.59 in liver and muscle, respectively. Using the small effect size of muscle changes (alpha = 0.05, power = 0.80), the required sample size to detect organ-specific differences in MRS measurements is 28. To account for a potential drop-out rate of 15%, the sample size was set to 32.

Clinical routine laboratory examinations and other blood sample analyses will be performed on 100 samples. This number of participants was chosen to reach sufficient power for detecting differences in gut metagenome analysis. Large inter-individual differences are usually observed in the composition of fecal microbiomes. Small differences in alpha diversity (effect size 0.55) between two groups of 50 individuals can be detected with an 80% statistical power (85). Missing values are commonly encountered in fecal microbiome evaluations (85). Accounting for missing data and sufficient numbers to quantify bacteria abundance at the species level for at least 50 individuals, we estimated that 100 subjects are needed for this part of the study (power = 0.80). This is based on a fecal metagenome analysis, which included missing values for more than 50% of 612 bacterial species out of 724 species detected (86).

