### Statistical analysis

The statistical analysis of the data will be performed using R software for statistical computing. Given the longitudinal design of our study with multiple repeated measurements, a mixed model for repeated measures will be used for quantitative variables. The *p*-values from linear-mixed models in the longitudinal data analysis will be adjusted with a *post-hoc* Tukey test. Missing data will be handled with complete case analyses for the dependent variables or imputed using the median for auxiliary variables with less than 20% missing values. Subgroups will be generated using demographic data (e.g., sex) or unsupervised clustering methods. The statistical models will be adjusted for potential confounders such as age, gender, or baseline body weights. A parsimonious approach will be used. If a covariate does not influence the variance of the model, it will be excluded from the model. We will use multivariate statistics for metabolomics or metagenomics, including unsupervised (e.g., principal component analysis) and supervised statistical methods (orthogonal partial least squares discriminant analysis, sparse partial least square discriminant analysis). In the case of multivariate analyses (e.g., microbiome data), the false discovery rate corrected *p*-value (*q*-value of 5%).

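### The data-driven covariate exclusion rule can drop a real confounder from the between-person microbiota and subgroup models; fix the covariate set in advance

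*Protocol article*

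**What the plan says.** The Statistical analysis section of the protocol article commits to adjustment: "The statistical models will be adjusted for potential confounders such as age, gender, or baseline body weights". Two sentences follow that qualify it: "A parsimonious approach will be used", and then "If a covariate does not influence the variance of the model, it will be excluded from the model". No test, threshold or measure of influence is given, and no covariate is named as one that must stay. The same section plans subgroups from demographic data (sex is the example) or from unsupervised clustering.

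The last item under Aims is an association between people: "we will measure if various metabolic and physiological changes, as described above, correlate to individual gut microbiota profiles". The Study design section describes a "prospective, monocentric, single-arm interventional study using a two-stage design", so covariates are not balanced by randomisation in such comparisons. The sample is 100 in total, 32 of whom have the MRI measurements. The Sample size calculation section plans for "sufficient numbers to quantify bacteria abundance at the species level for at least 50 individuals".

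**The concern.** Confounding depends on two relations: covariate with outcome, and covariate with exposure. The rule looks only at what a covariate adds to the fitted model, judges that in the same data, and then reads the p-values as if the model had been fixed beforehand. With 32 to 100 people, a moderate true confounder will often seem to add little and be removed.

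At stake is how the microbiota results are read. An association that only reflects age, sex or body weight could be reported as a link between bacteria and the response to fasting. Because the rule runs model by model, different outcomes could also be adjusted for different covariates, which makes their associations hard to compare. The planned false discovery rate control at 5% does not repair this: it handles the number of tests and takes each input p-value as valid.

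**Working it through.** **The plan's own figure.** No stated figure is tied to the exclusion rule. The nearest is 80% power for a between-person difference in alpha diversity of 0.55 SD with 50 per group. Normal approximation, two-sided 0.05: 0.55 × √(50/2) = 2.75, and Φ(2.75 − 1.96) = Φ(0.79) = 0.785. A two-sample t calculation gives 0.777. The plan's figure is reproduced to within rounding and is not in dispute.

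**Within-person changes.** For person i the change is Y(i, after) − Y(i, before). An additive effect of a covariate that is fixed over time cancels in that difference. A mixed model on balanced data gave identical time contrasts and standard errors with and without age. A simulated pre-post test omitting such a covariate had type I error of 0.047 to 0.052.

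**Between-person associations: inputs.** From the article: n = 32 (MRI subgroup), at least 50 (species-level data) and 100 (all). Alpha is 0.05, taken as two-sided. Assumed, because the article does not give them:
- b, the correlation of covariate C with outcome Y;
- ρ, the correlation of C with microbiota feature X;
- the form of the rule.

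X has no effect on Y given C, so every rejection is a false positive. Each cell has 20,000 runs; the Monte Carlo standard error near 5% is √(0.05 × 0.95 / 20,000) = 0.0015.

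**Check by hand (n = 100, ρ = 0.5, b = 0.2).**
- Without adjustment, the induced X–Y correlation is 0.5 × 0.2 = 0.10, so z ≈ 0.10 × √100 = 1.0. The rejection rate is Φ(−0.96) + Φ(−2.96) ≈ 0.170; simulated 0.167.
- With X in the model, the covariate's own z ≈ 0.2 × √(100 × 0.75 / 0.96) = 1.77. It is kept with probability about Φ(1.77 − 1.96) ≈ 0.42; simulated 0.41.

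**Rule read as: drop C when its p >= 0.05 with X in the model.** Type I error, with the share of samples that keep C in brackets:

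| ρ | b | n = 32 | n = 50 | n = 100 |
|---|---|---|---|---|
| 0.1 | 0.2 | 0.057 (0.19) | 0.057 (0.28) | 0.053 (0.51) |
| 0.1 | 0.3 | 0.055 (0.38) | 0.055 (0.56) | 0.053 (0.86) |
| 0.3 | 0.2 | 0.064 (0.18) | 0.071 (0.26) | 0.077 (0.48) |
| 0.3 | 0.3 | 0.077 (0.35) | 0.075 (0.53) | 0.066 (0.83) |
| 0.5 | 0.2 | 0.090 (0.15) | 0.101 (0.22) | 0.123 (0.41) |
| 0.5 | 0.3 | 0.118 (0.30) | 0.125 (0.45) | 0.114 (0.75) |

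A second run over b = 0.2 to 0.4 gave 5.4-7.8% at ρ = 0.3 and 7.0-13.2% at ρ = 0.5 across the three sample sizes. At ρ = 0.1 to 0.2 the range is about 5-6.5%. A strong confounder is safe in the full sample: at b = 0.5 and n = 100 it is kept in about 100% of samples, and the error is 0.051 to 0.052 at ρ = 0.3 to 0.5.

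**Other readings of the rule.**
- Joint test with a looser cut (drop at p >= 0.20): at most 0.090 for ρ up to 0.5.
- C screened on its own relation to Y, cut 0.05: 0.044 to 0.061 for ρ = 0.1 to 0.5, and at most 0.068 at ρ = 0.7 (12,000 runs per cell).
- C always kept: 0.047 to 0.053 in every cell.

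The two tests differ for a simple reason. In a joint model the coefficients of X and C compete, so C tends to be dropped just when X has absorbed its effect. Under a separate screen, C is dropped when its sample relation to Y is small, and then the spurious X–Y association is small too.

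**The case against.** The strongest case on the other side has four parts.

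- **The mechanism is assumed.** The article states no p-value, no cut-off and no joint test, and under a separate screen the inflation nearly vanishes. This stands, and is why the size is given as a range over readings. It does not clear the rule: exclusion from the model most naturally means a check on the fitted model, which is the less favourable reading.
- **The scope is partly inferred.** The rule precedes the separate list of multivariate methods (principal components, discriminant analyses), and the aim speaks of correlation without specifying an adjusted regression. This stands in part. The point covers covariate-adjusted between-person models only. The adjustment sentence, however, speaks of the statistical models generally and makes no exception for microbiota.
- **The criterion may sit in an analysis plan that is not shown.** A missing threshold alone would not be a finding. What the article does state is that named potential confounders may be removed according to the data.
- **A covariate that truly explains no outcome variance is not a confounder.** Correct, but the rule acts on a sample estimate, which often misses moderate confounders at these sample sizes.

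A reader might infer that the rule necessarily under-adjusts the microbiota associations and inflates their error. The documents do not support that: harm needs a covariate related to both microbiota and outcome that the rule wrongly discards. A reader might also quote the 12-26% found at a covariate-microbiota correlation of 0.7, but nothing in the article supports a correlation that high.

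**Conclusion.** The concern holds in conditional form. The rule can leave residual confounding in between-person associations and can make adjustment differ across outcomes; whether it does so depends on correlations and a cut-off that the article does not give. Under the least favourable plausible reading, with covariate-microbiota correlations of 0.3 to 0.5 and confounder-outcome correlations of 0.2 to 0.4, a nominal 5% test runs at about 5-13%. With weak covariate-microbiota correlation or a separate screen it stays close to nominal. Subgroup comparisons were not simulated separately; the same reasoning applies with group membership in the place of the microbiota feature.

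The primary body-composition changes against baseline are not affected, so the point does not touch the main conclusion of the trial. It is worth acting on because the remedy is nearly free.

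**What to change.** For covariate-adjusted between-person models, replace the exclusion rule with a fixed set: age, sex and baseline body weight, kept whatever their p-value or share of variance. Omit any variable that itself defines the comparison, such as sex in a comparison of men and women. Report any reduced model only as a sensitivity analysis. The within-person time contrasts need no change.

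The cost is a change of wording and up to three degrees of freedom. At n = 32 the residual degrees of freedom in a one-exposure model fall from 30 to 27. If the covariates were pure noise, the standard error would rise by a factor of about √(31/28) = 1.05, and at n = 100 by about √(99/96) = 1.02. A covariate correlated 0.5 with the microbiota feature adds a further factor of up to 1/√(1 − 0.25) = 1.15, partly offset when that covariate explains outcome variance. No new data are needed.

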#### Gut microbiota composition

Stool samples will be collected for shotgun metagenomics to determine the fecal microbiota composition in all participants prior to fasting and from the first spontaneous stool after the fasting period as previously described (6). We will evaluate microbial composition by identifying species-specific marker genes and functional potential by profiling microbial metabolic pathways and other molecular functions as described in other published fecal microbiome studies (77). The study of carbohydrate metabolism will be complemented by a carbohydrate-active enzyme (CAZy) profiling method that is currently in development at european molecular biology laboratory (EMBL) Heidelberg. All raw microbial data will be made available on public repositories.

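### OPLS-DA and sPLS-DA in standard form ignore the before/after pairing of this single-arm trial; fasting contrasts need a within-person version and person-level validation

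*Protocol article*

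**What the plan says.** All references are to the protocol article.

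- *Study design*: the trial is a "prospective, monocentric, single-arm interventional study using a two-stage design".
- *Gut microbiota composition*: stool is collected "in all participants prior to fasting and from the first spontaneous stool after the fasting period".
- *Statistical analysis*: because measurements are repeated, "a mixed model for repeated measures will be used for quantitative variables". Metabolomics and metagenomics get a separate set of multivariate tools: unsupervised methods such as principal component analysis, and "supervised statistical methods (orthogonal partial least squares discriminant analysis, sparse partial least square discriminant analysis". A q-value of 5% is given for multivariate analyses. The section states neither the classes to be discriminated nor a paired version.
- *Statistical analysis*, on possible other classes: "Subgroups will be generated using demographic data (e.g., sex) or unsupervised clustering methods".
- *Sample size calculation*: "Large inter-individual differences are usually observed in the composition of fecal microbiomes". The microbiome figure reads: "Small differences in alpha diversity (effect size 0.55) between two groups of 50 individuals can be detected with an 80% statistical power".

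**The concern.** The fasting effect can only be estimated by comparing people with themselves. For single quantitative variables the plan does this, through the mixed model. For the high-dimensional data it names two classifiers that, in standard form, see a set of samples with class labels and no link between the two samples of one person. If the classes are before and after, stable differences between people act as noise, although the design would allow them to be removed.

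A second, separate issue applies to any discriminant model with many features and few samples: its fitted separation says little, because it can also separate random data. A false discovery rate controls a list of p-values, not a fitted discriminant model.

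At stake are the metabolome and microbiome results. The primary MRI body-composition endpoints are unaffected.

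**Working it through.** **1. The plan's own figure.** Two independent groups of 50, d = 0.55, two-sided alpha 0.05 (stated for the MRI/MRS calculation, assumed here): z = 0.55 × √(50/2) − 1.96 = 2.75 − 1.96 = 0.79, which gives power of 78.5%. Inverting, n = 2 × (1.96 + 0.84)² / 0.55², or 52 per group. The stated 80% with 50 per group is thus reproduced approximately, as a comparison of independent groups. It concerns alpha diversity, and the discriminant analyses have no stated figure.

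**2. What pairing is worth for one feature.** Let each sample have SD 1 and let the two samples of a person correlate at rho. The mean change has variance 2(1 − rho)/n. An analysis that ignores pairing takes it as 2/n. The standard error it uses is therefore too large by a factor of 1/√(1 − rho): 1.00 at rho 0, 1.20 at 0.3, 1.41 at 0.5 and 2.24 at 0.8. The article gives no rho, so all these values are assumptions. Simulated power of t-tests with 100 pairs and an assumed shift of 0.3 SD (20,000 replicates):

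| rho | unpaired | paired |
|---|---|---|
| 0 | 55.3% | 55.1% |
| 0.3 | 56.4% | 70.7% |
| 0.5 | 57.9% | 84.5% |
| 0.8 | 62.9% | 99.6% |

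At the plan's d = 0.55 with 100 pairs and rho 0.5, the figures are 99.6% and above 99.9%, so nothing of note is lost.

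**3. The discriminant model.** Sparse PLS-DA was simulated with two components, 50 features kept and 5-fold cross-validation with whole persons in a fold. Inputs: 100 pairs (the planned total) and 724 features (the species count cited in the sample size section). Assumed: 20 features shifted by 0.3 SD. Accuracy over repeated runs:

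| rho | standard | within-person (multilevel) |
|---|---|---|
| 0.5 | 0.64 to 0.66 | 0.79 to 0.80 |
| 0.8 | 0.71 to 0.72 | 0.95 to 0.96 |

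The within-person version judges each sample relative to its partner. That is the information the standard version leaves unused.

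For the metabolome the article gives no feature count. With an assumed 1,000 features and 32 people, the gain is absent at rho 0.5 (0.56 against 0.55) and clear at 0.8 (0.60 against 0.82).

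**4. Pure noise, 100 pairs, 724 features.**

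- In-sample accuracy with all features: 1.00, 1.00 and 0.97 at rho 0, 0.5 and 0.8 for the standard model, and 1.00 throughout for the multilevel model. Samples from entirely different people also give 1.00.
- In-sample with 50 features kept: the standard model falls from 0.94 (rho 0) to 0.76 (rho 0.8); the multilevel model stays at 0.99 to 1.00.
- Cross-validation with whole persons in a fold: 0.47 to 0.54 for both, as it should be.
- Cross-validation splitting samples regardless of person: 0.10 to 0.31 for the standard model at rho 0.5 to 0.8, and 0.82 to 0.92 for the multilevel model.

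Noise separation therefore comes from the number of features relative to samples. Pairing does not cause it, and using the pairing does not cure it. Person-level validation does.

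OPLS-DA was not run separately. With one response it is a rotation of PLS and gives the same predictions at equal total components.

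**The case against.** The strongest reply is that the article only lists method families. It does not say that paired samples are treated as independent, it leaves the classes open, and the same section plans subgroups by sex or clustering, for which the standard methods are right. It recognises the repeated measurements. The multilevel form is a routine option of sPLS-DA, and an article commonly leaves such settings, and the validation scheme, to a fuller document. All of this stands as far as it goes: before/after as the classes is an inference, and missing validation detail is not an error. What remains is that the methods named do not, by default, fit the contrast on which the trial rests, and that the microbiome sample size is also framed as two separate groups.

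Stronger readings are tempting but not supported:

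- *That ignoring the pairing creates false separation.* It does not. It lowers in-sample separation of noise, and for a single variable it makes the test conservative (type I error 0.7% at rho 0.5 with 50 pairs).
- *That cross-validation will split the samples of a person.* The article says nothing on folds. With the standard model, such splitting would push accuracy on noise below chance, not above it.
- *That much of the fasting signal will be lost.* This depends on an unstated correlation and on unstated effects, and the loss is negligible for one variable at d = 0.55 with 100 pairs.
- *That the metabolome and microbiome aims rest on these models alone.* Unsupervised methods and corrected p-values are also planned.

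The feature count is uncertain too. Dropping the 612 species with more than 50% missing values leaves 724 − 612 = 112, fewer than the 200 samples, and in-sample separation of noise is then weaker.

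**Conclusion.** The point holds in a limited form. For before/after contrasts, the standard versions of the named methods are less efficient than a readily available alternative. Under the assumed inputs, person-wise accuracy is about 0.65 against 0.80 at a correlation of 0.5, and about 0.72 against 0.95 at 0.8. The gap narrows as the correlation falls. These figures rest on assumed correlations, on 20 features shifted by 0.3 SD, and on before and after being the classes.

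Separately, fitted separation is no evidence for either version when features are many relative to samples, and the 5% q-value does not change that. The change should be made, but it concerns secondary analyses and does not show that the plan states something false.

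**What to change.** Add to the Statistical analysis section:

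- State which classes each discriminant analysis separates.
- For contrasts between time points, use the multilevel (within-person) version of sPLS-DA, or OPLS on within-person differences.
- Keep all samples of a participant in one cross-validation fold. This is essential with the multilevel version, where splitting by sample gives about 0.9 on pure noise.
- Test significance by permuting time labels within participant.
- Report cross-validated error, not only the fitted score plot.
- Keep the standard version for between-person subgroups such as sex.

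The cost is a few sentences in the plan and a few lines of R using a standard option. The downside is that participants with only one sample drop out of this analysis, so their number should be reported.
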